#### My Knee Education (control)

Participants in the control condition are provided with a URL to access ‘My Knee Education’, a website containing only the educational information provided in the intervention within the ‘My Knee Education’ section with any reference to the intervention exercise program removed and replaced with general exercise and physical activity recommendations, like those available in current Internet-based Australian OA consumers resources. The control site does not contain an exercise program. All material within the website has been specifically developed for this study. After randomisation, participants receive an email, from the study co-ordinator, containing details of how to access the website (the URL and their unique username and password). Participants are asked to access the website at home, on their own device within 7 days, read the educational information provided and implement any exercise and physical activity recommendations as they see fit. Participants are instructed that they can view the website as often as they require. At the same time participants receive their access email they also receive a welcome SMS prompting them to access the website.

### Outcomes

Outcome measures are self-reported. The primary time point is 24-weeks after baseline. Table 2 summarises all measures captured.

**Table 2 Tab2:**
[figure not shown]
Schedule of enrolment, intervention, and assessments

*BMI* Body Mass Index, *EARS* Exercise Adherence Rating Scale, *NRS* numeric rating scale, *WOMAC* The Western Ontario and McMaster Universities Osteoarthritis Index, *KOOS* Knee Osteoarthritis Outcome Score, *ADL* Activity of Daily Living, *AQoL2* Assessment of Quality of Life Instrument, *PASE* Physical Activity scale for the elderly, *ASE* Arthritis Self Efficacy scale, *SEE* Self- efficacy for exercise scale, *SMS* Short Message Service

#### Descriptive and other measures

Age, sex, education level, current employment status, co-morbid conditions, duration of knee OA symptoms, laterality of symptoms, previous treatments and medications, problems in other joints, residential postcode and self-reported height and body mass are obtained at baseline. Body mass index is calculated using height and weight measures.

#### Primary outcomes

Primary outcomes are collected at baseline and 24-weeks.

*Overall knee pain*: Average overall knee pain in the past week is self-assessed using a 11-point numeric rating scale (NRS) [62] with terminal descriptors of ‘no pain’ (score 0) and ‘extreme pain’ (score 10).

*Physical function*: Limitations with physical functioning over the past week are measured by extracting the Physical Function subscale of the Western Ontario and McMaster Universities Osteoarthritis Index (WOMAC) from the Activity of Daily Living subscale of the Knee Injury and Osteoarthritis Outcome Score (KOOS) [63], which contains the WOMAC questions. It is a self-report measure with established validity, reliability and responsiveness in knee OA [64]. The physical function subscale contains 17 questions with response captured on a 5-point scale with terminal descriptors 0 = “none” to 4 = “extreme”. Total score ranges from 0 to 68 with lower scores indicating worse functioning.

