#### Data analysis

Analyses comparing the two groups will be performed by the statistician in a blinded fashion using all available data from all randomised participants according to the intention-to-treat principle. Should the amount of missing data for an outcome be greater than 5%, multiple imputation will be conducted, and the method reported. The primary analysis will analyse the multiply imputed datasets. Demographic and baseline characteristics of participants will be summarised as appropriate (means and standard deviations for continuous variables that appear to be distributed approximately symmetrically, medians and interquartile ranges for other continuous variables, counts and percentages for categorical variables) and will be inspected to assess baseline comparability of treatment groups. For continuous outcomes, differences will be compared between groups in either change (baseline minus follow up) or at 24 weeks using linear regression models adjusted for baseline levels of these outcomes. Model assumptions will be assessed using standard diagnostic plots. We will also calculate the proportion of participants in each group that show an improvement that reaches or exceeds the minimal clinically important difference in NRS pain (≥1.8 units) and in WOMAC function (≥6 units). For this and other binary outcomes, differences between groups will be compared using relative risks, calculated from logistic regression models.

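### The protocol states the direction of the WOMAC physical function score, a primary outcome, backwards relative to its own item coding

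*Protocol article*

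**What the plan says.** The physical function entry under Primary outcomes gives four facts about the score.

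- **Construct:** "Limitations with physical functioning over the past week are measured by extracting the Physical Function subscale" of the WOMAC, taken from the KOOS Activity of Daily Living items.
- **Items:** "The physical function subscale contains 17 questions with response captured on a 5-point scale".
- **Coding:** "with terminal descriptors 0 = “none” to 4 = “extreme".
- **Total and direction:** "Total score ranges from 0 to 68 with lower scores indicating worse functioning".

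The Data analysis section uses the score in two ways. For continuous outcomes, "differences will be compared between groups in either change (baseline minus follow up) or at 24 weeks", by linear regression adjusted for the baseline level. It also reports the proportion in each group with an "improvement that reaches or exceeds the minimal clinically important difference in NRS pain (≥1.8 units) and in WOMAC function (≥6 units").

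Two other scales matter for context. The pain NRS, the other primary outcome, runs from 0 (no pain) to 10 (extreme pain). The KOOS subscales listed under Secondary outcome measures run from 0 to 100, with 0 the worst.

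**The concern.** The item coding and the direction sentence disagree, and they describe one of the two primary outcomes. The direction sentence is the protocol's only explicit statement of which way this score runs.

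The responder rule asks for an improvement of at least 6 units but gives no sign. A programmer therefore has to decide whether a rise or a fall is an improvement, and the sentence that answers this gives the wrong answer for the coding printed beside it.

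The mix-up is plausible in practice. The items come from a KOOS subscale, and the KOOS scores in the same dataset run with 0 as worst, which is the direction the faulty sentence gives to the WOMAC total. If it were followed, a benefit on function could be reported as harm, and participants who got worse could be counted as responders.

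**Working it through.** **1. Direction from the stated coding.** Inputs: 17 items, each 0 (none) to 4 (extreme), measuring limitation (Primary outcomes).

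- No limitation on any item: 17 × 0 = 0.
- Extreme limitation on every item: 17 × 4 = 68.

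The range of 0 to 68 is reproduced. The best possible score is 0 and the worst is 68, the opposite of the printed direction.

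**2. What the responder rule does on this coding.** Take a participant who improves from 34 to 28. Baseline minus follow-up is 34 − 28 = +6, which meets the rule. A participant who worsens from 28 to 34 has −6 and does not. If a rise were taken as improvement, the two would swap places.

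**3. The plan's own sample size figures, to see whether they depend on direction.** Inputs (Sample size calculation): effect size 0.40, 80% power, two-sided 0.05, pre-post correlation r = 0.35, 15% loss, SD 11.7 for function.

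- Completers per arm, baseline-adjusted comparison: 2 × (1.96 + 0.84)² × (1 − 0.35²) / 0.40² = 86.1, rounded up to 87.
- Allowing for loss: 87 / 0.85 = 102.4, rounded up to 103 per arm, 206 in total. This matches the protocol.
- Power for 6 WOMAC units: the residual SD is 11.7 × √(1 − 0.35²) = 10.96, which gives 95.1% at 87 and 95.3% at 88 completers per arm. This matches the stated 95%.

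These calculations use only the absolute size of the difference, so score direction does not enter.

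**4. Size of the reversal if the sentence were followed (illustration).** From the protocol: SD 11.7, r = 0.35, effect 0.40 × 11.7 = 4.68 units. Assumed, because the protocol gives no figures: mean control improvement of 6, 8 or 10 units, normally distributed change, and the same SD at both times and in both groups.

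- SD of change = 11.7 × √(2 × (1 − 0.35)) = 13.34.
- Correct rule: P(change ≥ 6) = 1 − Φ((6 − mean) / 13.34).
- Reversed rule: P(change ≤ −6) = Φ((−6 − mean) / 13.34).

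Change is baseline minus follow-up, so positive values are improvement on the stated coding.

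| Mean improvement, control / intervention | Correct rule, control vs intervention | RR | Reversed rule, control vs intervention | RR |
|---|---|---|---|---|
| 6 / 10.68 | 50% vs 64% | 1.27 | 18% vs 11% | 0.57 |
| 8 / 12.68 | 56% vs 69% | 1.24 | 15% vs 8% | 0.55 |
| 10 / 14.68 | 62% vs 74% | 1.20 | 12% vs 6% | 0.53 |

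**5. Sensitivity to the assumed values.** With a 6-unit true difference and control improvements of 0, 3 and 6 units, the correct relative risks are 1.53, 1.43 and 1.35, and the reversed ones are 0.56, 0.52 and 0.48. The relative risk moves from above 1 to below 1 in every case tried.

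**The case against.** The strongest reply is that this is a drafting slip with no necessary effect on the analysis. Much of that stands.

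- The responder rule asks for an improvement and prints no signed cut-off. If the printed change formula is applied to the printed coding, the right participants are counted whatever the direction sentence says. Reversal needs an analyst to follow that sentence over the item anchors.
- The test is two-sided and the comparison is a baseline-adjusted regression, so the absolute estimate, the width of its interval and the p-value are the same either way. The responder proportion is a supplementary summary.
- The article has similar slips elsewhere. Under Process measures, three 7-point scales scored 1 to 7 have their upper anchor printed as 2.

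A reader might also infer a second contradiction: that defining change as baseline minus follow-up cannot coexist with lower scores being worse. The document does not support this. The same formula covers all continuous outcomes, including several where higher is better (KOOS subscales, AQoL, PASE, self-efficacy). For those, improvement is simply a negative value. The formula is a sign convention and does not settle the direction of any one scale.

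What the reply does not remove is the contradiction within the outcome description. The sentence is complete and legible, concerns a primary outcome, and is wrong for the coding given.

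**Conclusion.** The concern holds as an error in the description of a primary outcome. On the protocol's own coding, the WOMAC function total is higher when function is worse, and the text says the reverse. This follows from the Primary outcomes section alone and rests on no assumption beyond the absence of any described reverse scoring.

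The consequence is conditional. The sign of the function effect and the responder count could be read in reverse if the sentence were applied literally. The relative risks of about 1.20 to 1.27 turning into about 0.53 to 0.57 show how far that could go under the assumed control improvement of 6 to 10 units, normal change and a 0.40 SD effect. They are not a prediction.

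A reader might infer that the trial will mis-score function, or that its planned analysis is invalid. The document does not show that: it prescribes no reversed cut-off, and sample size, power, effect size in absolute terms and two-sided p-value are untouched.

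**What to change.** - In the physical function entry under Primary outcomes, change the end of the sentence so that it says higher scores indicate worse functioning.
- In Data analysis, define a WOMAC function responder as baseline minus follow-up of at least 6 on the raw 0 to 68 scale, that is, a fall in score of 6 or more.
- Check that the scoring code sums the items as coded 0 to 4 and treats a fall as improvement. If the code does reverse the score, say so and restate the change and the responder rule to match.

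The cost is one corrected sentence, one added definition and a check of the code. Data collection, sample size and the analysis model stay as they are.

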#### Secondary outcome measures

Self-reported secondary outcomes are measured at baseline and 24 weeks, unless indicated otherwise.

*Pain, function in sport and recreation and knee-related quality of life in the last week:* Additional subscales of the Knee Injury and Osteoarthritis Outcome Score (KOOS) are being measured [63] including i) pain (9-items), ii) function in sport and recreation (5-items) and iii) knee-related quality of life quality of life (4-items). Responses are provided on a 5-point scale. Scores will be calculated for each subscale and range from 0 to 100 with 0 indicating worst possible symptoms.

*Health-related quality of life:* The AQoL questionnaire (version AQoL-II) [65] is measuring health related quality of life. This is a 20-item measure with responses provided on a 5-point scale. Scores range from − 0.04 to 1.00 with 1 indicating full health-related quality of life.

*Physical activity*: The Physical Activity Scale for the Elderly [66] is being used to assess physical activity, over the previous week. This is a 10-item measure which collects responses for the frequency, duration, and intensity level of a range of activities typically chosen by older adults. Scores range 0 to > 400 with higher scores indicating greater levels of physical activity.

*Self-efficacy:* The Arthritis Self-Efficacy Scale [67] is being used to measure arthritis specific self-efficacy. Two subscales are being collected, self-efficacy for managing pain (5-items) and physical function self-efficacy (9-items) with responses provided on a 10-point scale. Scores for each subscale range from 1 to 10 with higher scores indicating greater self-efficacy.

*Exercise self-efficacy:* The Self-efficacy For Exercise (SEE) Scale is measuring exercise self-efficacy. This is a 9-item measure with responses provided on a 11-point scale. Scores range from 0 to 90 with higher scores indicates higher self-efficacy for exercise.

*Participant-perceived change overall due to treatment (24 week only)*: Participants rate their perceived change in their condition overall, since baseline, on a 7-point scale with terminal descriptors of 1 = “much worse” to 7 = “much better”. Scores of 6 (“moderately better”) and above will be considered to indicate improvement [68].

*Overall satisfaction (24 week only):* Participants rate their overall satisfaction with the digital resource(s) they accessed as part of the study on a 7-point scale with terminal descriptors of 1 = “very dissatisfied” to 7 = “very satisfied”. Scores range from 1 to 7 with higher scores indicating greater satisfaction.

#### Process measures

A range of process measures are assessed at 24-weeks, unless indicated otherwise.

*Exercise importance (baseline and 24-weeks)*: Participants will be asked the question “How important is it to you to do regular exercise to manage your knee condition?” Responses are collected on a 7-point scale with terminal descriptors 1 = ‘not at all important’ and 7 = ‘extremely important’. Scores range from 1 to 7, with higher scores indicating higher importance.

*Self-reported number of exercise days in the previous week:* Participants are asked “In the past week, how many days did you participate in exercise for your knee condition?” Scores range from 0 to 7.

*Adherence to prescribed home exercise:* Exercise Adherence Rating Scale (EARS) Section B is being used to measure adherence to prescribed home exercise [69]. This is a 6-item measure. Responses are collected on a 5-point scale. Scores range from 0 to 24 with higher score indicating better adherence.

*Perceived usefulness of study website*: Participants are asked to report their level of agreement with the statement “I thought the website I accessed as part of the study was useful in helping me manage my painful knee”. Responses will be collected on a 7-point scale with terminal descriptors 1 = ‘strongly disagree’ and 2 = ‘strongly agree’. Scores range from 1 to 7 with higher scores indicating higher perceived usefulness.

*Perceived usefulness of SMS exercise adherence support (intervention only)*: Participants are asked to report their level of agreement with the statement “I thought the mobile phone text messages I received were useful in helping me manage my painful knee”. Responses will be collected on a 7-point scale with terminal descriptors 1 = ‘strongly disagree’ and 2 = ‘strongly agree’. Scores range from 1 to 7 with higher scores indicating higher perceived usefulness.

*SMS frequency feedback (intervention only)*: Participants agreement with the statement “The number of text messages I received over the past 6 months was the right amount for me.” Responses will be collected on a 7-point scale with terminal descriptors 1 = ‘strongly disagree’ and 2 = ‘strongly agree’. Scores range from 1 to 7 with higher scores indicating higher agreement. Participants who select ≥3 will be asked ‘Did you receive too many or too few?’ with response collected via 1 = ‘too few’ or 2 = ‘too many’.

*Website access:* Participants are asked to estimate how many times they accessed their study website in: i) the first month of the study, and ii) month five of the study. Responses are collected in an open numerical field box.

*Exercise equipment purchased:* Participants will be asked if they purchased any exercise equipment to help them with their knee exercise. Participants who select ‘yes’ will be asked to estimate the cost of the equipment purchased in an open numerical field box.

*Website and SMS program data:* Interaction data will be collected from both websites and the SMS program such as website logins and SMS program ‘opt-outs’.

*Adverse events*: Any problem that participants believe was caused by the information received as part of the study and required them to seek treatment/take medications, and/or interfered with function for two or more days are recorded via questionnaire.

*Co-interventions:* Medications and other treatments for knee OA are recorded at 24 weeks using a custom-developed survey. This survey records the frequency of use of a range of pain and arthritis medications and co-interventions over the past 6 months.

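### The routing rule for the SMS-frequency item contradicts its own scale: neutral and agreeing respondents are asked whether texts were too many or too few, and the strongest disagreers are not

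*Protocol article*

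**What the plan says.** The Protocol article, Process measures, describes the item as "SMS frequency feedback (intervention only"), collected at 24 weeks. The statement to be rated is "The number of text messages I received over the past 6 months was the right amount for me". The direction of the scale is explicit: "Scores range from 1 to 7 with higher scores indicating higher agreement". The anchors are printed as a "7-point scale with terminal descriptors 1 = ‘strongly disagree’ and 2 = ‘strongly agree", so the upper anchor carries the number 2 on a scale that runs to 7.

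The routing rule reads: "Participants who select ≥3 will be asked". What they are asked is whether the texts were excessive or insufficient in number, and the answer is coded in two categories: "with response collected via 1 = ‘too few’ or 2 = ‘too many". No third option, such as about right, is listed. No other section of the article gives a different rule for this item.

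**The concern.** A follow-up on whether messages were too many or too few makes sense only for someone who has just said that the number was not right. On this scale those are the low scorers, yet the printed rule selects by a lower bound and so reaches the top of the agreement range.

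What is at stake is narrow. The SMS exercise adherence support section describes two to five messages a week, declining over time to limit burden, so frequency is a deliberate design feature. This follow-up is the only measure described that shows in which direction participants thought the frequency was wrong. According to the Procedures section, assessments are online surveys, so a routing error in the survey would run as programmed. The item is collected once, so a direction not asked for at 24 weeks has no later visit at which to be recovered.

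**Working it through.** No sample-size or power figure is involved. The check sets the rule against the scale, one response value at a time.

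**Inputs** (Protocol article, Process measures, unless stated otherwise)

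- Scale: 1 to 7, where 1 is strong disagreement and higher means more agreement that the number of texts was right.
- Trigger for the follow-up: score ≥3.
- Follow-up answers listed: too few, too many.
- Arm size: 206 / 2 = 103 (Sample size calculation).
- Loss to follow-up allowed for: 15% (Sample size calculation).

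**Step 1. Midpoint.** (1 + 7) / 2 = 4. Only the end points are labelled in the text, so calling 4 neutral, 1 to 3 the disagree side and 5 to 7 the agree side is an assumption based on symmetry.

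**Step 2. The printed rule applied to each score.**

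| Score | Meaning | Asked under ≥3? | Does the question apply? |
|---|---|---|---|
| 1 | strongest disagreement | no | yes |
| 2 | disagreement | no | yes |
| 3 | mild disagreement | yes | yes |
| 4 | midpoint | yes | no, or doubtful |
| 5 | agreement | yes | no |
| 6 | agreement | yes | no |
| 7 | strongest agreement | yes | no |

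Five of the seven values trigger the question. One of those five (score 3) lies on the disagree side. Two of the three disagree values (1 and 2) are skipped.

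**Step 3. The inequality turned round.** Under ≤3 the asked set is {1, 2, 3} and the skipped set is {4, 5, 6, 7}. This matches the purpose of the question.

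**Step 4. Does the misprinted anchor rescue the rule?** Taken literally, with 2 as strong agreement, a score of 3 or more would lie above the top anchor. The rule would still not select those who disagree. The rule would be coherent if low scores meant agreement, but the sentence on score direction excludes that.

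**Step 5. Number of participants.** At most 103 in the intervention arm. With the protocol's own loss allowance, 103 × (1 − 0.15) = 87.55, or about 88 at 24 weeks. The article gives no expected distribution of answers, so the share of follow-up answers from people to whom the question does not apply cannot be calculated.

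**The case against.** The strongest reply is that this is probably a slip in the article and not a fault in the survey. The same paragraphs print the upper anchor as 2 in three agreement items, while the exercise-importance item in Process measures and the satisfaction item in Secondary outcome measures correctly print 7. A ≥ typed for ≤ would fit that pattern. The live survey is not shown and may already use ≤3. This stands: the text is certainly inconsistent, but harm to the data depends on what was programmed.

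A reader might go further than the article allows in four ways.

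- **That the trial's conclusion on the acceptability of message frequency would be wrong.** The 1-to-7 rating is collected whatever the rule says, and SMS opt-outs are recorded separately under website and SMS program data. Only the directional follow-up is damaged.
- **That nobody who is dissatisfied is asked.** Score 3 is asked. The loss is confined to scores 1 and 2.
- **That satisfied users are forced to report a fault.** Two answer codes are listed, but the article does not say that an answer is mandatory. Answers from scores 4 to 7 can also be set aside at analysis, because the rating that triggered them is on record.
- **That ≤3 is established as the intended cut-off.** It is the most plausible reading, but ≤2 or ≤4 would also be coherent.

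It cannot be set aside as a detail left to an analysis plan. The article states a specific collection rule, and no later analysis can supply a direction that was never asked for.

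**Conclusion.** The point holds as a minor one. As printed, the rule contradicts the item's scale: it asks mild disagreers, neutral respondents and all who agree (3 to 7) and skips the strongest disagreers (1 and 2). If the survey runs that way, the direction of dissatisfaction with SMS frequency is missing for scores 1 and 2, and the answers collected are mixed with those of people to whom the question does not apply.

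The reach is one conditional sub-question of an intervention-only process measure, in at most 103 participants. No primary or secondary outcome, sample-size figure or between-group comparison depends on it. The conclusion about the text rests only on the stated scale direction and the stated trigger. The conclusion about the data rests on the further assumption, untestable from the article, that the live survey uses the printed rule.

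The upper anchor of 2 is a clerical slip. Each affected item goes on to say that scores run from 1 to 7, so the meaning is recoverable.

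**What to change.** 1. Check the branching logic of the live 24-week survey for this item.
2. Reverse the rule, in the survey if ≥3 is live and in the protocol text in any case, so that the disagree side is asked. The most plausible form is ≤3; the authors should confirm the cut-off they intended.
3. If ≥3 was live for any participants, report the follow-up only for respondents on the disagree side, and state that direction is missing for scores 1 and 2 collected before the correction.
4. As an editorial correction, print the upper anchor as 7 for strong agreement in the three agreement items (usefulness of the website, usefulness of the SMS support, SMS frequency).

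The cost is one check of the survey logic, at most one edit to it, and a few characters of text.
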